#### WP8: community film making and social media campaign

Around 15 adolescents (single-gendered groups and more females) will be supported to create three short films on experiences and risks around adolescent mental health, the potential for the school to affect mental health and solutions to safeguard their well-being. Films will be used in WP1–4 for engagement, education, advocacy and impact and to inform (1) a community and stakeholder’s event. Films will be used in WP1–4 for engagement, education, advocacy and impact, via (1) a community and stakeholder’s event to screen the films to promote shared understanding and solutions; (2) a social media education campaign targeting adolescents’ mental health literacy; and (3) an advocacy campaign targeting national-level policy-makers. Outcomes will include open access films and new knowledge on the feasibility and reach of community filmmaking for health education and advocacy campaigning for school mental health in India.

### Data analysis plan

#### WP1–5: Codesign/coadaptation

Workshop data will include audio/video recordings, facilitator notes and design materials (eg, maps, user journeys, reference ranking, annotated implementation and safeguarding protocols). Key workshop moments which informed an adaptation or new design component will be transcribed, supplemented with facilitator notes and accuracy checked by two facilitators. Workshop data from different stakeholder groups per focus (eg, intervention, implementation, safeguarding) will be integrated by WP leads. They will synthesise proposed modifications and report them as per FRAME^48^ to take forward to final approval stages in preparation for the feasibility study (described above).

#### WP1–5: feasibility study

School-level effects will be handled as fixed rather than random effects. Primary analysis will be analysis of covariance where outcomes at 3 months are regressed on the baseline value and any relevant covariates/factors as age, sex, school, participant characteristics. The analysis will be supported by a two-level mixed-effects model where measures at two timepoints are nested within participants. If further to this analysis, a model is required to examine the relationship between the change in measure over time and the initial measure level, then Bloomqvist’s method will be employed. Process evaluations will be analysed using framework analysis^60^ or thematic analysis.^61^ The implementation achievements in each school will be quantified per intervention and as a systems approach, and actions associated with success will be identified, drawing on the CFIR^45^ and as per Hudson *et al*.^44^

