### Year 2: feasibility testing

Lay counsellors will be from the local areas, have at least a master’s qualification in psychology or a related discipline and experience in working with young people and/or schools. Prior to the launch of the feasibility study, they will receive full training over 3 months by a clinical psychologist on the team, supported by another team member experienced in training lay counsellors. Trainees will deliver multiple mock sessions of intervention delivery to support readiness for delivery in schools and quality control. The feasibility study will run in eight schools, with three randomly assigned to waitlist. The four interventions will run in parallel in schools. Lay counsellors will complete weekly monitoring logs of intervention delivery in each school, including logging of modifications made (as per FRAME^48^) and will have weekly supervision by clinical team members. Fidelity monitoring will be undertaken by a team of trained data collection assistants who have been heavily involved in the intervention development stage and will be highly familiar with the implementation protocol. Fidelity monitoring reports will be discussed frequently with the research manager to identify needs for lay counsellor action/support or intervention modification (see WP5).

We have established preliminary feasibility indicators for each intervention, which will be updated when interventions are finalised. Feasibility indicators which will be common across WP1–4 interventions are: meeting recruitment and retention rates, delivery as intended, measure completion and no significant adverse effects. We will adopt a ‘traffic light’ system for recruitment and retention as follows: red—if rates below 50% (say) then will not proceed; amber—if rates 50%–65% then proceed if there are plans to improve; green—above 65% proceed to definitive trial. Mixed-methods process and evaluation data will be secured for all interventions from adolescents, teachers, parents and lay counsellors to explore: perceived usefulness of the interventions; implementation challenges; unintended negative effects; safeguarding challenges; the process of change and intervention development needs. Evaluation outcomes will inform intervention improvements and parameters for a definitive trial.

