### Sample size calculation

The planned sample for the feasibility study by intervention is detailed in table 2. The minimum recommended sample size for a feasibility study is 30.^49^ The smallest group of participants are teachers (for the WP2 intervention). To secure a sample of 30, we will need to recruit a minimum of 8 schools, from which we will then be able to recruit approximately n=960 grade 9 adolescents (for WP1 intervention). Given this adolescent sample size, we have been able to calculate power in relation to WP1, where a key aim is to test two candidate primary outcomes measures—the Strengths and Difficulties Questionnaire (SDQ)^50^ and the Revised Child Anxiety and Depression Scale (RCADS).^51^ SDQ is an emotional and behavioural screening tool, culturally validated in India and used widely in adolescent mental health research. RCADS measures anxiety and depression and demonstrates excellent sensitivity to change. A translated RCADS has been used with Indian populations^52^ but full cultural validity needs to be established. As this will be an important tool to strengthen Indian mental health research, we will conduct a full validation study in parallel to the codesign stage. We have determined via a UK school feasibility trial^53^ that the change in SDQ had a SD of 2.8 points. Assuming 80% recruitment, comparing the mean changes in SDQ from 480 participants from the intervention group with 288 from the waitlist group using a 1% significance level has more than 98% power to detect a difference of 1 point on the SDQ Scale. Around 960 adolescents will be approached for WP1. At 65% recruitment, the power remains over 95%. This calculation is based on an analysis of variance approach, that is, regressing the change in SDQ on the intervention status (intervention or waiting list). The power achieved from an analysis of covariance approach, which regresses the final SDQ Score on baseline and intervention status, should be similar. Should the mechanism of the WP1 intervention be similar across population subgroups, we can therefore show good power. There may, however, be differences in the operation of the intervention between subgroups, such as government versus private schools. In that case, assuming an even division of samples, the power becomes 85% with 80% recruitment and 78% with 65% recruitment. A significance level of 1% is used rather than 5% since the sensitivity of the outcome measures is sought to be compared—that is, the SDQ will be compared in sensitivity in this setting with the RCADS.

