
**Table 2 T2:** Planned sample size for each intervention in the feasibility study

WP	Intervention	N	Sample
1	Universal curriculum adolescent mental health programme	960	Grade 9 15–16 year olds from 8 schools (120 per school)
2	Teacher education programme	32	Grade 9 teachers (4 per school)
3	School climate intervention	8 schools	To be defined following intervention selection
4	Parental mental literacy intervention	960 sets of parents	Aim to reach all parents/carers of WP1 participants

WP, work packages.

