## Discussion

In India, a key contextual determinant of adolescent mental health is the nature of schooling.^13–22^ This codesign and feasibility study is an important step towards an integrated, multicomponent whole-school approach to adolescent mental health in Indian secondary schools. School-delivered well-being programmes have the potential to exceed the reach and scalability of mental healthcare systems in LMICs.^8–10^ By targeting adolescent anxiety and depression, the interventions produced in SAMA will contribute to public mental health approaches to common adolescent mental health conditions in India, and, by promoting well-being factors, can inform health promotion strategies. Unique outcomes of the study include rich data on what Indian schools, and their communities, need and want from a whole-school approach to mental health as well insights into what aspects of international programmes need particular cultural adaptation. Mental health literacy among Indian adolescents, parents and teachers has been reported as low.^18–20^ Our study will generate new knowledge on whether programmes developed in other countries, with likely different conceptualisations of mental health and responses to it, can be successfully coadapted to be acceptable and helpful in Indian schools. By adopting a randomised controlled waitlist design, the study will generate a solid evidence base for progression to a randomised controlled trial and inform understanding of the acceptability and rigour of data collection instruments and process evaluations in complex intervention studies in Indian schools. To date, school initiatives in India have mostly targeted physical health and life skills.^24–27^ Drawing on the expertise of an international, interdisciplinary team, this study aims to contribute to the evidence base about what works in Indian schools to support adolescent mental health, and in particular, to reduce the prevalence and severity of adolescent anxiety and depression.

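### With whole schools randomised and school entered as a fixed factor, the primary ANCOVA has no separately identified intervention coefficient, and the computable alternatives ignore between-school variance

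*Protocol article*

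**What the plan says.** Allocation is by school. Under Year 2: feasibility testing: "The feasibility study will run in eight schools, with three randomly assigned to waitlist". The Discussion presents this as a randomised comparison: "By adopting a randomised controlled waitlist design".

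Under Data analysis plan, WP1–5: feasibility study, the plan makes three statements:

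- "School-level effects will be handled as fixed rather than random effects".
- In the primary ANCOVA, "outcomes at 3 months are regressed on the baseline value and any relevant covariates/factors as age, sex, school, participant characteristics".
- The supporting analysis is a "two-level mixed-effects model where measures at two timepoints are nested within participants".

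The Sample size calculation describes the ANCOVA differently, as one that "regresses the final SDQ Score on baseline and intervention status", with no school term. Its power figures come from a comparison of 480 with 288 individual pupils.

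**The concern.** Fixed cluster effects work when treatment varies within the cluster. Here it does not: intervention status is a property of the school. Once each school has its own fixed term, nothing is left from which to estimate a separate intervention effect. The plan does not merely leave the choice open, because it rejects random school effects by name.

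At stake is the one between-arm comparison that the article powers and calls primary. Followed literally, the model returns an arbitrary contrast. Repaired in the obvious ways (averaging the fixed schools, or dropping them), it returns an estimate whose standard error treats pupils as independently randomised. Either could be carried forward as a parameter for the definitive trial.

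**Working it through.** **Inputs from the article.** 8 schools, 5 intervention and 3 waitlist. Table 2 gives "Grade 9 15–16 year olds from 8 schools (120 per school"), so 80% recruitment means 96 per school: 5 × 96 = 480 and 3 × 96 = 288. SD of SDQ change 2.8, difference 1 point, significance level 1%. **Assumed:** ICC of 0, 0.01, 0.02 or 0.05 (none is given), and two-sided testing (not stated).

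**1. The plan's own power figure.** With pupils independent, z = 1 / (2.8 × √(1/480 + 1/288)) = 4.79. Power = Φ(4.79 − 2.576) = 98.7%. At 65% recruitment (390 vs 234), z = 4.32 and power is 95.9%. Both stated figures (more than 98%, over 95%) reproduce, under a model with no school effect.

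**2. Identifiability of the primary model.** The arm indicator equals the sum of the five intervention-school indicators. A design matrix with intercept, baseline, age, sex, arm and 7 school dummies has 12 columns and rank 11. Deleting the arm column leaves 11 columns and still rank 11, so arm adds no information. This is algebra and does not depend on ICC, SD or sample size. In one simulated data set with a true effect of −1, changing which pair of school dummies was omitted moved the printed intervention coefficient from about +0.02 to −3.13.

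**3. What the computable alternatives do.** The true variance of a school mean is 2.8² × (ICC + (1 − ICC)/96). An analysis with averaged fixed schools uses only 2.8² × (1 − ICC)/96. The ratio of true to assumed variance is R = (1 + 95 × ICC)/(1 − ICC). An analysis without school terms has R ≈ 1 + 95 × ICC. The false-positive rate at nominal 1% is 2 × [1 − Φ(2.576/√R)].

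| ICC (assumed) | R, fixed schools averaged | False positives | R, school dropped | False positives |
|---|---|---|---|---|
| 0.01 | 1.97 | 6.7% | 1.95 | 6.5% |
| 0.02 | 2.96 | 13.4% | 2.90 | 13.0% |
| 0.05 | 6.05 | 29.5% | 5.75 | 28.3% |

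Simulation (4000 runs per ICC, no true effect) agrees: about 6-7%, 12-13% and 30-31%. A t-test on the eight school means stayed at about 1% throughout.

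**4. The supporting model.** With fixed school main effects, time and arm-by-time, the matrix has 10 columns and rank 10, so arm-by-time is estimable. Adding school-by-time as fixed terms gives 17 columns and rank 16, and the aliasing returns. As described, the model's only levels are timepoints and participants, so between-school variation in change is left out of its standard error.

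**5. Power once school is the unit.** SE = √[2.8² × (ICC + (1 − ICC)/96) × (1/5 + 1/3)]. The critical t on 6 df at two-sided 1% is 3.707, and power is from the noncentral t with noncentrality 1/SE.

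| ICC (assumed) | SE | 1/SE | Power for 1 point |
|---|---|---|---|
| 0 | 0.209 | 4.79 | 80% |
| 0.01 | 0.291 | 3.43 | 47% |
| 0.02 | 0.355 | 2.81 | 31% |
| 0.05 | 0.500 | 2.00 | 14% |

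The first row shows that 6 degrees of freedom alone, without any clustering, lower power from 98.7% to 80%.

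**The case against.** **The wording is permissive.** School appears in an open list, "regressed on the baseline value and any relevant covariates/factors as age, sex, school, participant characteristics", so it might be left out. School-level effects might mean features such as government versus private, and the sample-size section gives an ANCOVA without school. On that reading the model is estimable. This has some force, but the plan's opening sentence commits to fixed school effects and school itself is a listed factor. Without school, the fault becomes ignored clustering, with the error rates in step 3.

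**The effect is not beyond estimation.** A reader might infer that no intervention-versus-waitlist contrast can be obtained. That goes too far. The mean of the five fixed intervention-school effects minus the mean of the three waitlist ones can be computed. What is missing is a separate intervention coefficient and a standard error that reflects the randomisation of schools.

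**Other stronger readings.** A reader might count it as a fault that the ANCOVA sentence does not name intervention status. In a condensed article it is not one, since the sample-size section supplies it. A reader might also infer that the school climate work package has one outcome per school, so that school terms would saturate its model. The article does not say so: Table 2 leaves that sample to be defined, and Table 1 lists secondary outcomes such as perceived stigma and perceived support, which could be measured on individuals.

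**It is a feasibility study.** No progression rule uses the ANCOVA p-value. This lowers the stakes but does not remove them, because the article states a 1% test with power, names a primary analysis and claims a solid evidence base for a later trial.

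**Conclusion.** The point holds as a fault in a stated rule, not as missing detail. With school as a fixed factor, the primary ANCOVA has no separately identified intervention coefficient, and this rests on the allocation alone. The contrasts that can be computed instead reject a true null at about 6-7%, 12-13% and 30% under a nominal 1% test. Those rates rest on assumed ICCs of 0.01, 0.02 and 0.05, 96 pupils in each school and equal school sizes. At an ICC of 0 there would be no inflation. The supporting model does not repair this.

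It would be wrong to infer that the feasibility conclusions fail. The traffic-light thresholds for recruitment and retention do not depend on this model.

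**What to change.** In the data analysis plan for WP1–5:

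- Remove school identity as a fixed factor, name intervention status in the model and state that school is the randomised unit.
- Primary analysis: compare school means of the 3-month score, adjusted for baseline, age and sex, five schools against three, by t-test on 8 − 2 = 6 df. If school type is added as a school-level covariate, 5 df remain.
- A mixed model with a random school effect and small-sample degrees of freedom is an alternative. It is not equivalent, and with eight schools the school variance may be estimated at zero.
- A permutation test over the 56 possible allocations can only be supportive. Its smallest p-value is 1/56 = 0.018, so it can never reach the 1% level.
- Add school as a level, including school-by-time, to the supporting mixed model.

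In the Sample size calculation, restate power for the school-level analysis over a declared range of ICCs, and present the effect estimates as exploratory.

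**Cost.** No new data are needed. Confidence intervals widen, and the claim of more than 98% power has to go: at 80% recruitment it becomes about 80%, 47%, 31% and 14% at ICCs of 0, 0.01, 0.02 and 0.05.

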### School recruitment

We will recruit eight schools in Kolar and Bangalore to participate in both the codesign and feasibility stages of SAMA (WP1–6). School recruitment will be facilitated by the Karnataka State Primary and Secondary Education Ministry and the Karnataka State Secondary School Headmaster’s Association. We will recruit two school types (government and low-cost private) to identify school factors that may affect feasibility. Schools will be eligible to take part in SAMA if they endorse the delivery of WP1–6 in their schools, including participation in codesign. WP1 intervention feasibility testing will be with a new grade 9 cohort not involved in codesign.

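### The primary ANCOVA takes school as a fixed factor although whole schools are randomised, so it has no separately identified arm effect and is not the model that was powered

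*Protocol article*

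**What the plan says.** Allocation is by school. Under Year 2: feasibility testing: "The feasibility study will run in eight schools, with three randomly assigned to waitlist". That leaves five intervention schools, and every pupil in a school is in the same arm.

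The data analysis plan for the WP1–5 feasibility study then says: "School-level effects will be handled as fixed rather than random effects". In the next sentence the primary analysis is an ANCOVA in which 3-month outcomes are "regressed on the baseline value and any relevant covariates/factors as age, sex, school, participant characteristics".

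The sample size section has another model in mind. Its power is for "comparing the mean changes in SDQ from 480 participants from the intervention group with 288 from the waitlist group using a 1% significance level", and the ANCOVA it describes as similar in power is one that "regresses the final SDQ Score on baseline and intervention status". Neither contains a school term.

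**The concern.** In a trial that randomises schools, the information about the intervention lies in differences between schools. A fixed effect for each school absorbs all of those differences and leaves only variation among pupils within the same school, where there is no contrast between arms. The primary model as described therefore cannot deliver the randomised comparison as a coefficient. The analyst has to improvise, either by building a contrast from the school effects or by leaving school out. Both give a number, and both attach a standard error that treats the eight schools as if they would not differ without the intervention. The power statement and the 1% significance level then describe a precision that the design does not have.

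**Working it through.** **Inputs.** From the article: 8 schools, 5 v 3; 120 pupils approached per school (Table 2); 80% recruitment, so 96 per school, 480 v 288; SD of SDQ change 2.8; difference 1 point; significance level 1%. Assumed: ICC of 0.01, 0.03 or 0.05 for the change or baseline-adjusted outcome, with 2.8 as the total SD.

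**1. The stated power.** SE = 2.8 × √(1/480 + 1/288) = 0.209. Then 1/0.209 = 4.79, and 4.79 − 2.576 = 2.21, which gives 98.7% power (two-sided). At 65% recruitment (390 v 234), SE = 0.232 and power is 95.9%. Both agree with the article (more than 98%, over 95%). They belong to a pupil-level model with no school term and no clustering.

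**2. The model in the analysis section.** Let S₁…S₈ be the school indicators, with schools 1–5 in the intervention arm. Then arm = S₁ + S₂ + S₃ + S₄ + S₅ exactly.
- Intercept, baseline, arm and 7 school indicators: 10 columns, rank 9.
- With age and sex added: 12 columns, rank 11. The residual sum of squares of arm given the other terms is zero to machine precision.
- Baseline, age, sex and arm without school: 5 columns, rank 5.

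The aliasing is exact at any sample size and needs no assumed ICC.

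**3. What can still be recovered.** The mean of the five intervention-school effects minus the mean of the three waitlist-school effects is estimable. With equal school sizes its SE is 2.8 × √(1/(5×96) + 1/(3×96)) = 0.209, the same as in step 1. It contains within-school variation only. The true variance of the contrast exceeds the reported one by the factor 1 + 96 × ICC/(1 − ICC). The actual error of a nominal 1% test is 2 × [1 − Φ(2.576/√factor)].

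| Assumed ICC | Factor | Actual error |
|---|---|---|
| 0.01 | 1.97 | 6.6% |
| 0.03 | 3.97 | 19.6% |
| 0.05 | 6.05 | 29.5% |

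**4. Dropping school and treating pupils as independent.** The factor becomes 1 + 95 × ICC = 1.95, 3.85 and 5.75, and the actual error is 6.5%, 18.9% and 28.3%. This is no repair.

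**5. An analysis that respects the allocation.** For school means, SE = 2.8 × √[(ICC + (1 − ICC)/96) × (1/5 + 1/3)], with t(0.975, 6 df) = 2.447.

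| Assumed ICC | SE | 95% half-width |
|---|---|---|
| 0.01 | 0.29 | 0.71 |
| 0.03 | 0.41 | 1.00 |
| 0.05 | 0.50 | 1.22 |

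Power for 1 point at the two-sided 1% level on 6 df is 80% at ICC 0, 47% at 0.01 and 14% at 0.05.

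**The case against.** The best defence is that the effect is not lost. The 5 v 3 contrast of fixed school effects can be computed, and its SE equals the one behind the stated power. That is correct as arithmetic. But the contrast is conditional on these eight schools: pre-existing school differences are counted as intervention effect, and its SE ignores them. It supports no inference beyond those schools.

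A second defence is that the covariate list is permissive and that the sample size section names intervention status. The list is loose, but the sentence before it is unconditional and school is named. This is a stated choice that conflicts with another section, not detail left to a later document.

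Third, the supporting model of two time points within participants can estimate arm-by-time beside fixed school main effects (10 columns, rank 10). It cannot once school-by-time is added (17 columns, rank 16), and it has no school-level random term, so it too ignores clustering of change.

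Fourth, this is a feasibility study, and its numerical progression rule concerns recruitment and retention, not a p-value. That limits the consequence. The article nonetheless powers a between-arm test at 1% and presents the randomised waitlist design as evidence for progression.

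A reader might infer more than the text supports:
- That the reported effect would be one intervention school minus one waitlist school. This needs software to drop a school indicator and the analyst to report what remains; nothing in the article says so.
- That the arm term has been forgotten. The sample size section names it, so its absence from the covariate list is shorthand.
- That the school climate model (WP3) is saturated. Table 2 leaves that sample to be defined.
- That the school-type question is aliased too. The article says "We will recruit two school types (government and low-cost private) to identify school factors that may affect feasibility", and nothing makes this a coefficient in the ANCOVA.

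**Conclusion.** The point holds, and the analysis section is wrong as written. With school as a fixed factor, the primary ANCOVA has no separately identified arm effect, and it differs from the ANCOVA to which the power statement refers. This follows from the allocation alone. The claim should not be stretched to say that no between-arm number can be obtained: the five-against-three contrast exists, but its SE of 0.209 leaves out between-school variation.

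The size of the harm rests on assumed ICCs, since the article gives none. A nominal 1% error of about 7%, 20% and 30% at ICCs of 0.01, 0.03 and 0.05 also assumes equal school sizes of 96 and a total SD of 2.8. At an ICC of zero there is no inflation. The traffic-light progression decision is untouched; what is affected is any estimate, interval or test comparing arms.

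**What to change.** Reconcile the sample size section with the analysis section so that one primary model is described in both, for example: *School will not be entered as a fixed factor in any between-arm comparison. The 3-month outcome will be compared between arms, adjusting for baseline, age and sex, with allowance for clustering by school.*

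Then choose one of two analyses:
- a regression on baseline, age, sex and arm with a random school intercept and a small-sample degrees-of-freedom correction; or
- a comparison of covariate-adjusted school means, 5 v 3 on 6 df.

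These are not interchangeable when school sizes differ or when the school variance is estimated as zero. A zero estimate would be expected in about 20% of balanced trials at ICC 0.01 and 58% at ICC 0, and the corrected degrees of freedom can then go well above 6. The school-level analysis is the safer choice.

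Report the estimate with a 95% confidence interval. State that the power in the sample size section applies to a pupil-level comparison with no clustering by school. Fixed school effects can stay for questions answered within schools.

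The cost is wording only, with no change to recruitment or data collection. The price is an interval as wide as the design implies: a half-width of about 0.7 to 1.2 SDQ points for assumed ICCs of 0.01 to 0.05, against a target difference of 1 point.
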